### Sample size

Sample size was calculated based on the only existing trial [23]. For the primary outcome, retention in treatment, the hazard ratio for the group of patients randomized to ILC compared with treatment as usual was 0.62. We obtained a total sample size of 137 with a power of 80% and an alpha-level of 0.05. We conducted a post hoc power analysis for secondary outcomes (self-reported offending, self-reported substance use). For these measures, we set α = 0.01 due to multiple hypothesis testing and assessed power with three waves of measurement (baseline, three and six months post-randomization) and assumed a correlation of 0.5 between repeated measures. The resulting Cohen’s f that could be measured with a power of 0.95 was 0.16, corresponding to a small to moderate effect size. Finally, for number of offences, we calculated power based on a Poisson distribution; assuming a base-rate of 0.85 offences, the study will have 95% power to measure an incremental risk ratio of 1.43.

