One program that has been tested in a single multicenter trial is the Impulsive Lifestyle Counselling (ILC) program [23, 24], which was developed as an add-on to treatment for substance use disorders with co-morbid antisocial personality disorder in outpatient settings. ILC is a six-session psycho-educative program delivered face-to-face that focuses on increasing self-understanding and on linking impulsive and destructive behaviors to their immediate negative consequences, supporting motivation for change (see Table 1). The trial showed that random assignment to ILC was associated with a reduction in dropout and substance use behaviors [23, 24]. However, the comparison treatment was not standardized and was based on a “treatment as usual” approach. It is well-documented that the less defined and structured the comparison condition is, the higher the estimated efficacy of treatment [25]. Another limitation was that the participants in the trial were very heterogeneous, representing both opioid, alcohol, cannabis, and stimulant users [23, 24]. An advantage to such a heterogeneous sample is that it prioritizes external validity [26, 27], as treatment units for people with substance use disorders often serve people with poly-substance use. However, this comes at a cost because such trials are unable to inform clinicians and administrators about the value of the intervention for more specific target groups.

**Table 1 Tab1:** Headings of the sessions of Impulsive Lifestyle Counselling

Session	Content
1. Assessment	AdultMap assessment of strengths and challenges
2. Treatment plant	Collaborative development of a treatment plan, including the ILC program
3. Introduction	Dreams, goals, and four areas of an impulsive lifestyle (self-indulgence, breaking rules, interpersonal intrusiveness, and irresponsibility).
4. The TAC-model: Triggers, Reactions, Consequences	Learn about the connections between triggers, behaviors and consequences and begin to apply the model.
5. Streetwise pride and self-worth	Understand the pride associated with antisocial behavior, deceptiveness and crime and think about alternative sources of pride and self-worth
6. Values	Identify values that support or under-mine change in externalizing behavior.

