#### Main objectives

To test whether the combination of ILC/MOVE-I will improve treatment retention compared with MOVE-I for patients with externalizing behavior enrolled in OAT.To use case controls from the Register of Drug Abusers in Treatment to examine if ILC and MOVE-I are superior to treatment as usual in municipalities where ILC and MOVE-I have not been implemented in OAT, as measured by number of offences leading to conviction and number of emergency room contacts 12 months post-randomization.

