#### ILC

ILC is a brief, highly structured psychoeducational program targeting impulsive and destructive behaviors. The original manual is available in English (DOI: 10.13140/RG.2.2.27332.01927). In the two first sessions, the focus is on assessment and establishing treatment goals. Following these two sessions, the patient proceeds to six pre-defined sessions, each covering a different topic (see Table 1). Following ILC, participants will receive six of the sessions of MOVE-I. The content of these six sessions will depend on what themes in the MOVE-I manual are deemed relevant at this stage in treatment by the counsellor and the participant.

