## Discussion

This trial will be only the second to evaluate the efficacy of a novel psychoeducational program for externalizing behavior problems, ILC. This trial will assess the impact of the program on retention in treatment, severity of drug use, and days of criminal offending in patients with externalizing problems undergoing OAT.

By providing participants with vouchers for attendance, we maximize the likelihood that they will attend sessions regardless of randomization assignment, thus reducing the risk that lack of compliance will mask or exaggerate any real differences between the two conditions. Further, by having a manualized, evidence-based comparison for ILC, we set the standard for showing efficacy higher than in the previous trial.

If ILC turns out to be superior to MOVE-I, it will have strong implications for patients in OAT with externalizing behavior problems. ILC has been shown to be very easy to learn and implement, and no special training is required for clinicians with some experience working with patients with substance use disorders.

Certain limitations are unavoidable, even though they are already known at this point. The influx of new patients into the sites is limited, so it is not possible to include only new admissions.

A further limitation is that the total number of patients is unlikely to be high enough for analysis of moderators of outcome.

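### The 80% power rests on a hazard ratio against unstandardised treatment as usual, carried over unadjusted to a comparison with manualised MOVE-I that the protocol itself describes as a harder test

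*Protocol article*

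**What the plan says.** On sizing, the Sample size section states "Sample size was calculated based on the only existing trial". It reports that "the hazard ratio for the group of patients randomized to ILC compared with treatment as usual was 0.62", and continues: "We obtained a total sample size of 137 with a power of 80% and an alpha-level of 0.05". It gives no other hazard ratio, no allowance for a different control and no reason for expecting 0.62 to carry over.

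On the planned comparison, Main objectives reads "To test whether the combination of ILC/MOVE-I will improve treatment retention compared with MOVE-I". The control is therefore a manual-based course of motivational interviewing and cognitive behavioural therapy, not usual care.

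On what the change of control does, the Background describes the earlier trial's comparison as unstandardised and says it is well documented that "the less defined and structured the comparison condition is, the higher the estimated efficacy of treatment". The Discussion says of the manualised, evidence-based control that "we set the standard for showing efficacy higher than in the previous trial".

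**The concern.** The effect used for sizing belongs to a different contrast from the one being tested. Changing the comparator is not a fault in itself, and the protocol presents it as a strength. The difficulty is that two sections say in which direction the change works, while the sample size calculation proceeds as if it made no difference. If the effect against MOVE-I is smaller than the effect against treatment as usual, as the Background's reasoning implies, the power of the primary test is below 80%.

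What is at stake is how a non-significant result would be read. A reader who sees 80% in the protocol would take such a result as an adequately powered negative finding for ILC over MOVE-I. That reading is justified only for an effect as strong as the one seen against the weaker control. The Discussion's limitations cover patient influx and moderator analyses, not power for the primary comparison, and no interim analysis is planned at which the assumption could be revisited.

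**Working it through.** **Inputs.** From Sample size: hazard ratio 0.62, power 80%, alpha 0.05, total 137. From Statistical analyses: Cox regression. Assumed, because not stated: a two-sided test and 1:1 allocation. The Randomization section aims for equal distribution within each centre, which is consistent with 1:1.

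**Step 1: reproduce the plan's figure.** Schoenfeld's formula for the required number of events is

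d = 4 × (1.960 + 0.842)² / (ln HR)²

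With ln 0.62 = −0.478, d = 4 × 7.849 / 0.2285 = 137.4. This agrees with 137, so 0.62 entered the calculation unchanged. The alternatives fit less well: Freedman's formula gives 143 two-sided, and one-sided tests give 109 (Schoenfeld) or 113 (Freedman). The formula counts events, whereas the protocol gives 137 as participants.

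**Step 2: power at weaker effects, granting 137 events.**

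Power = Φ( |ln HR| × √137 / 2 − 1.960 ), with √137 / 2 = 5.852

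| HR against MOVE-I | abs(ln HR) × 5.852 | minus 1.960 | Power | Events for 80% |
|---|---|---|---|---|
| 0.62 | 2.798 | 0.838 | 79.9% | 138 |
| 0.65 | 2.521 | 0.561 | 71.3% | 170 |
| 0.70 | 2.087 | 0.127 | 55.1% | 247 |
| 0.75 | 1.684 | −0.276 | 39.1% | 380 |
| 0.80 | 1.306 | −0.654 | 25.7% | 631 |

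The hazard ratios from 0.65 to 0.80 are assumed values. The document gives none for ILC/MOVE-I against MOVE-I.

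**Step 3: the same loss as a share of the log hazard ratio.** Losing 10% of ln 0.62 gives HR 0.65 and power 71%. Losing 25% gives 0.70 and 55% (55.5% at the unrounded 0.699). Losing half gives 0.79 and 29%.

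**Step 4: dependence on events.** The figures in Step 2 need all 137 participants to have the event. Under Outcomes, patients who complete treatment successfully are censored, and so are those still in treatment when the trial ends, so fewer events are to be expected. As an illustration only, suppose half of the participants drop out, about 69 events. Then √69 / 2 = 4.153. Power at HR 0.62 is Φ(0.478 × 4.153 − 1.960) = Φ(0.025), about 51%. The hazard ratio detectable with 80% power is exp(−2.802 / 4.153), about 0.51.

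**The case against.** The strongest defence is that power is always conditional on an assumed effect. The section names the effect, its comparator and its source, and no hazard ratio against MOVE-I is available. Any trial with a new control must extrapolate, and the higher bar is disclosed in the Discussion. This stands in part: the 80% is not an arithmetic error, and the attribution to treatment as usual is already in the text. What it leaves unanswered is that the calculation neither adjusts for nor justifies an assumption that two other sections undercut.

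It could also be said that 0.62 is a target difference. The section presents it as the earlier trial's result, not as a minimum worthwhile effect.

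A reader might look for more reasons why the contrast has narrowed. The document does not support them:

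- **Population.** The earlier sample mixed users of several substances. The Background says this limits what can be learned about specific groups, not that it inflated the effect. An opioid-only sample could show more or less.
- **Vouchers and reminders.** The Discussion says attendance vouchers guard against differences being either masked or exaggerated. That gives no direction.
- **Shared sessions.** The ILC section says "Following ILC, participants will receive six of the sessions of MOVE-I", although the Abstract gives nine. But ILC "was developed as an add-on to treatment for substance use disorders with co-morbid antisocial personality disorder in outpatient settings", so treatment common to both arms is not necessarily new here.

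Only the comparator argument has a direction stated in the protocol.

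**Conclusion.** The point holds as one about an unadjusted and unjustified effect size. The stated 80% depends on the treatment-as-usual effect being fully retained against MOVE-I, and the protocol's own reasoning suggests that this is too favourable. The direction is documented; the size is not. Across assumed hazard ratios of 0.65 to 0.80, power runs from 71% down to 26%, given 137 events, a two-sided 0.05 test and 1:1 allocation. With fewer events these are upper bounds.

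Three stronger conclusions might be inferred and should not be. The first is that the 80% is miscalculated; it reproduces. The second is that a non-significant result is likely. With 137 events power falls below 50% only when the hazard ratio exceeds about 0.715 (exp(−1.960 / 5.852)), and the document does not say how far the effect will shrink. The third is that 0.62 is the weakest effect detectable with 80% power. That is true only with about 137 events, and the document gives 137 as participants.

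This should be changed before results are known, but it is a matter of disclosure and interpretation and does not invalidate the design.

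**What to change.** Keep the sample size and revise the Sample size section in three ways:

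1. State that 80% power holds only if the hazard ratio of 0.62 seen against treatment as usual is fully retained against MOVE-I and about 137 dropout events occur.
2. Replace the single figure with power for ILC/MOVE-I against MOVE-I at hazard ratios nearer 1, for example 0.65, 0.70, 0.75 and 0.80, calculated at the expected number of events. State that number and its basis. Any statement of the smallest detectable effect should be tied to the same number.
3. Add, there or in the Discussion, that a non-significant primary result will be interpreted from the confidence interval for the hazard ratio and not as evidence that ILC adds nothing to MOVE-I.

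The cost is a few sentences and a short table, with no additional participants. The downside is that the stated power becomes less favourable.

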**Methods:**

The study is a multicenter, randomized, controlled, superiority clinical trial. Participants will be a total of 137 hard-to-treat individuals enrolled in opioid agonist treatment (OAT). Participants will be randomized to either a standard treatment (14 sessions of individual manual-based cognitive behavioral therapy and motivational interviewing (MOVE-I)) or six sessions of ILC followed by nine sessions of MOVE-I. All participants will receive personalized text reminders prior to each session and vouchers for attendance, as well as medication as needed. The primary outcome is retention in treatment. Secondary measures include severity of drug use and days of criminal offending for profit three and nine months post-randomization. A secondary aim is, through a case-control study, to investigate whether participants in the trial differ from patients receiving treatment as usual in municipalities where ILC and MOVE-I have not been implemented in OAT. This will be done by comparing number of offences leading to conviction 12 months post-randomization recorded in the national criminal justice register and number of emergency room contacts 12 months post-randomization recorded in the national hospital register.

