Compared with patients with other substance use disorders, people with opioid use disorders have the highest risk of criminal activity, psychiatric comorbidity, poly-substance use, infections, such as HIV and hepatitis C [10, 11], as well as excess mortality [12, 13] and a high degree of somatic comorbidity [14]. However, this is primarily due to the fact that opioid use disorders represent the most severe end of the substance use disorder spectrum, and while opioid use disorder is associated with antisocial personality traits, this is mostly as part of its overall relationship with a general propensity for substance use disorders [15]. Once opioid use disorder is established, however, criminal offending may be reduced by the provision of medication assisted treatment [16].

The dual burden of using a drug with particularly heavy consequences and externalizing behavior problems may put some patients at very high risk for a range of adverse outcomes. A considerable barrier to benefitting from treatment is staying in contact with the system for a sufficient time; around 30% of patients drop out of psychosocial treatment across types of substances and treatment, and dropout rates are even higher for more disadvantaged patients and treatments that demand time and concentration [17, 18]. Furthermore, a growing body of evidence suggests that patients with externalizing and criminal behavior are particularly hard to retain in treatment and offer relevant help but that improved retention and treatment effects may be associated with substantially lower costs of crime [19, 20]. Thus, improving retention and outcomes for people with externalizing disorders who enroll in OAT is of crucial importance.

One way to improve retention and outcomes is the use of contingency management (CM) in the form of voucher-based reinforcement therapy [21]. However, the evidence base for specially tailored programs to serve the needs of people with opioid use disorder who are high on externalizing problems is extremely limited. A recent narrative review based on a small handful of studies indicated that cognitive behavioral therapy and CM, or milieu therapy alone or in combination with other interventions, have not been differentially effective for patients with opioid use disorder and antisocial personality disorder [22].

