### Study setting and recruitment

Participants (*N* = 137) will be recruited from OAT in four outpatient municipal treatment centers situated in four Danish cities: Herning, Randers, Aarhus, and Aabenraa. Both current patients and new admissions will be invited to participate. The study is situated at the Centre for Alcohol and Drug Research, Aarhus University.

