### Outcomes

The primary outcome measure is retention in OAT. Retention in treatment will be calculated starting on the date of randomization and until the patient is discharged or the trial ends. Patients who are registered as having completed a successful course of treatment will be considered censored at the date of discharge, as was the case in the pilot trial [23]. Any reason for discharge, other than completed treatment, will be considered dropout, even if discharge is on patient request. In general, discharge occurs when the patient no longer receive any services. Note that practices may vary slightly between sites in terms of their practices when discharging patients. As researchers we are legally and practically unable to influence these decisions. None of the participating sites discontinue OAT against patients’ wishes, neither because of substance use, nor because of failure to attend treatment. Only the present episode is considered in this trial (i.e., the episode that is initiated or ongoing at the time of randomization).

The secondary outcomes are 1) substance use other than prescribed medications (AdultMAP) [1]; 2) self-reported days in the last month with offences for profit (AdultMAP); 3) substance use and everyday functioning (concentration, planning, keeping appointments, sleeping, eating habits, cleaning etc.) in the last month (AdultMap) and last week (WOM); 4) social interaction with individuals (family, friends, acquaintances) with non-criminal behavior and/or with no substance abuse in the last month (AdultMap); 5) employment/educational activities in the last month (AdultMap).

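### The sample size of 137 matches the number of dropout events needed for the stated 80% power, but is used as the number of participants

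*Protocol article*

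**What the plan says.** The Sample size section rests on one previous trial, in which "the hazard ratio for the group of patients randomized to ILC compared with treatment as usual was 0.62". From that it concludes: "We obtained a total sample size of 137 with a power of 80% and an alpha-level of 0.05". It names no formula, sidedness, allocation ratio, expected number of events or expected proportion of participants with an event.

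Elsewhere 137 is a head count. The Methods part of the Abstract gives it as the total number of individuals in the trial. Study setting and recruitment gives N = 137 for participants who "will be recruited from OAT in four outpatient municipal treatment centers", and adds that both current patients and new admissions are invited.

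The Outcomes section defines the primary outcome as time from randomization to discharge from OAT or the end of the trial. Discharge for any reason other than completed treatment is an event, including discharge that the patient asks for. Patients who complete treatment successfully are censored. The section also says "None of the participating sites discontinue OAT" against the patient's wish.

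Statistical analyses specifies Cox regression, run 365 days after the last patient is randomized.

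**The concern.** In a Cox comparison, power depends on the number of events, not on the number of people enrolled. A calculation from a hazard ratio, alpha and power alone yields events. A further step, division by the expected proportion with an event, is needed to reach participants. Here the stated inputs lead straight to the stated total, with no room for that step.

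This is the only justification given for the trial's size on its primary outcome. If the 80% stands as written, a non-significant result would be read as coming from a trial with a four-in-five chance of detecting a hazard ratio of 0.62, and perhaps as evidence that Impulsive Lifestyle Counselling (ILC) does not improve retention. The real chance could be well below that.

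**Working it through.** **Inputs from the article.** Hazard ratio 0.62, power 80%, alpha 0.05, total 137 (Sample size); Cox regression (Statistical analyses); completers censored, follow-up to discharge or trial end (Outcomes).

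**Assumptions.** Two-sided test, since sidedness is not stated. 1:1 allocation, since minimization between two arms is described without a numerical ratio. The proportion with an event is varied, since none is given.

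**Step 1: reproduce 137.** Schoenfeld, 1:1:

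d = 4 × (z for alpha + z for power)² / (ln HR)²

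- z values: 1.960 + 0.8416 = 2.8016; squared, 7.849
- ln 0.62 = −0.4780; squared, 0.2285
- d = 4 × 7.849 / 0.2285 = 137.4 events

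This is the stated figure, or 138 if rounded up. The Freedman formula gives 142.6 events, which does not match and would make the shortfall slightly larger.

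**Step 2: what 137 participants deliver.** With a proportion p having an event, d = 137 × p, and

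power = Φ( √(d/4) × |ln HR| − z for alpha )

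Example for p = 0.5: d = 68.5; √(68.5/4) = 4.138; 4.138 × 0.4780 = 1.978; 1.978 − 1.960 = 0.018; Φ(0.018) = 0.507.

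| Assumed dropout by cut-off | Events | Power, two-sided 5% | Power, one-sided 5% |
|---|---|---|---|
| 30% | 41.1 | 33% | 46% |
| 50% | 68.5 | 51% | 63% |
| 70% | 95.9 | 65% | 76% |
| 80% | 109.6 | 71% | 80% |
| 90% | 123.3 | 76% | 84% |
| 100% | 137 | 80% | 88% |

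**Step 3: where two-sided power passes 50%.** This needs √(d/4) × 0.4780 = 1.960, so d = 4 × 1.960² / 0.2285 = 67.2 events, or 67.2/137 = 49% dropout.

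**Step 4: one-sided reading.** With z = 1.645, d = 4 × (1.645 + 0.8416)² / 0.2285 = 108.2 events, or 108.2/137 = 79% dropout.

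**The case against.** The strongest reply is that the match proves less than it seems to. The article names no formula, and 137.4 has to be rounded down to give 137. Another route reaches the same total: a one-sided 5% test needs 109 events, and 109/0.8 = 136.25, which rounds up to 137. The full protocol, which the article condenses, might contain an event assumption. This stands to a degree. A reader might infer that the authors mistook events for participants, but the documents show only that the two numbers coincide. The alternative route needs two inputs the article does not state, a one-sided test and about 80% dropout. Under a two-sided test, no proportion below 100% reconciles 137 participants with 80% power, so an unpublished proportion could not rescue the claim.

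A second reply concerns the likely size of the shortfall. A reader might take the Background figure, "around 30% of patients drop out of psychosocial treatment across types of substances and treatment", and conclude that the trial has 33% power and will more likely than not miss the planned effect. The documents do not support that. The figure concerns psychosocial treatment, not discharge from OAT. The Background says rates are higher in more disadvantaged patients and that patients with externalizing behavior are hard to retain, and this trial enrols such patients. Patient-requested discharge counts as an event, and everyone randomized before the last patient can be followed for more than 365 days. Against this, patients already settled in OAT are eligible and sites do not end OAT against a patient's wish. The rate could lie on either side of 30%, but nothing here makes universal dropout plausible.

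A reader might also add that 0.62 is optimistic, because it came from a comparison with treatment as usual and the Background argues that "the less defined and structured the comparison condition is, the higher the estimated efficacy of treatment". That is a judgement about the size of the effect, separate from this arithmetic. The Discussion openly accepts that the manualized comparator sets a higher standard.

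**Conclusion.** The point holds. The article's inputs yield 137.4 events under the standard two-sided, 1:1 calculation, while 137 is the number of people to be recruited. Because the design censors completers and patients still in OAT, the stated 80% power holds only if all 137 drop out. Below that, power at a hazard ratio of 0.62 falls to 76% at 90% dropout, 71% at 80%, 65% at 70%, 51% at 50% and 33% at 30%. If the test was meant to be one-sided at 5%, about 79% would still have to drop out.

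The conclusion rests on the two-sided test, 1:1 allocation and the Schoenfeld approximation. The dropout proportions are assumed and only show the range. It cannot be said that the trial is more likely than not to miss the planned effect: that is true only below about 49% dropout, and the documents give no OAT discharge rate.

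**What to change.** Restate the primary-outcome part of the Sample size section:

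- Give about 137 (138 rounded up) as the number of dropout events required for a hazard ratio of 0.62 with 80% power, and name the formula, sidedness and allocation ratio.
- State the proportion of participants expected to have an event by the cut-off, one year after the last randomization, and the basis for it.
- Replace the 80% with the power that 137 participants deliver at that proportion, with a short range around it.
- Say that a non-significant result will be interpreted through the confidence interval of the hazard ratio, not as absence of an effect.

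If a one-sided test with a high event proportion was in fact assumed, the paragraph should say so and justify both.

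The change is to wording only. It asks for no added enrolment and alters neither the outcome nor the analysis. The cost is a less favourable stated power.
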